### Quality control

2.8

Researchers must strictly follow the study protocol and comply with standard operating procedures. All clinical observations and findings must be verified to ensure the effective implementation of quality control and quality assurance systems throughout the study. Quality control measures must be implemented at every stage of data processing to ensure the reliability and accuracy of the data.

Prior to study initiation, all participating researchers must undergo comprehensive training, including guidance on relevant data, operational procedures, and assigned responsibilities. Given that the study involves assessments using scales related to anxiety and depression, all researchers must be trained by a psychiatrist, and qualified professionals in psychological assessment must be included in the research team. This ensures consistency in clinical data collection and guarantees that all data are recorded objectively, accurately, and truthfully in the medical records and CRFs. Throughout the study, monitors from the lead research institution will conduct regular audits of source clinical data at study sites to ensure strict adherence to the study protocol. If a subject’s treatment regimen is modified during the study, investigators must record the details and reasons for the change and continue follow-up as planned. During data analysis, the principal investigator and statistical experts will allocate each subject to the appropriate analysis set.

Researchers should foster participant confidence in the treatment and maintain effective communication to ensure a clear understanding of the study requirements, thereby improving adherence. Participant adherence will be monitored using the medication count method. Before each medication dispensing, remaining study drugs and empty packaging will be collected. Adherence will be calculated as follows: [(prescribed amount - unused amount)/prescribed amount] × 100%. Good adherence: 80%-120%, Poor adherence: <80%.

Measures taken to reduce bias: Researchers must strictly adhere to the inclusion and exclusion criteria specified in the protocol, enroll participants consecutively, and maintain follow-up until the end of the study to minimize selection bias. Researchers should remind participants to take medication as prescribed, assess outcomes objectively, and strictly comply with laboratory procedures for sample testing to reduce information bias. Potential confounding factors should be addressed using stratified and multivariate analyses to reduce confounding bias.

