#### Blinding

2.3.2

This study adopts a double-blind design. The first level blinding corresponds to the group codes linked to medication numbers (Group A, Group B), while the second level pertains to the treatments assigned to each code (SGJY group or placebo control group). Both levels of blinding will be documented by statisticians independent of trial analysis. Two sealed copies of the blinding records will be maintained separately by the principal research center. These blinding records must remain unopened throughout the study period. The first unblinding for the statistical analyst will conduct after data lock, and the second after completion of the statistical analysis. Emergency envelopes may only be opened in the event of a medical emergency (serious adverse event, rapidly deteriorating condition). Each envelope will contain designated fields for the signature, date, and reason for unblinding by the person who opens it. Cases withdrawn due to therapeutic reasons should not be unblinded. The unblinded case materials must be kept intact.

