### Statistical analysis

2.7

Statistical analyses were performed using SAS version 9.3 (SAS Institute Inc., USA) and included baseline characteristics, efficacy, and safety outcomes. A p-value of < 0.05 was considered statistically significant. The efficacy analysis will follow the intention-to-treat (ITT) principle. The Full Analysis Set (FAS) includes all randomized patients, excluding those who severely violated the inclusion criteria or did not receive any assigned treatment. Baseline characteristics will be analyzed within this set to assess comparability. The Per-Protocol Set (PPS) includes patients who completed the planned treatment regimen, whereas the Safety Set (SS) consists of patients who received at least one dose of the study treatment and underwent safety evaluation. Efficacy analysis will be primarily applied to the FSA and PPS. Safety evaluations will be performed using the SS.

For primary and secondary outcomes, continuous data will be analyzed using the t-test or Mann-Whitney U test; categorical data will be assessed using the Chi-squared test or Fisher’s exact test; and ordinal data will be evaluated using the Mann-Whitney U test. To account for potential center effects in this multicenter trial, analyses will be stratified by study site. Efficacy will be evaluated using the Cochran-Mantel-Haenszel (CMH) test to adjust for inter-center variability.

If baseline characteristics between groups are imbalanced, confounding factors that are difficult to control or unmeasured may be included as covariates in an analysis of covariance (ANCOVA) or logistic regression model. Between-group differences in efficacy will be assessed using least-squares means (LSMEANs) and their 95% confidence intervals to minimize the impact of confounding factors.

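### As written, patients can be assigned to analysis sets after the A/B codes are open to the analyst, and neither the FAS nor the PPS is named as the set that decides efficacy

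*Protocol article*

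**What the plan says.** All references are to the protocol article.

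- **When sets are assigned, and by whom** (section 2.8, Quality control): "During data analysis, the principal investigator and statistical experts will allocate each subject to the appropriate analysis set".
- **When codes are opened** (section 2.3.2, Blinding): "The first unblinding for the statistical analyst will conduct after data lock, and the second after completion of the statistical analysis". The first level is the Group A/Group B code. The second level says which code is SGJY and which is placebo.
- **Data lock** (section 2.6.3): the principal investigator and the statistical analysts lock the data while blinded. No set assignment is mentioned there.
- **Set rules** (section 2.7, Statistical analysis): "The efficacy analysis will follow the intention-to-treat (ITT) principle". The FAS is all randomised patients, "excluding those who severely violated the inclusion criteria or did not receive any assigned treatment". For the other efficacy set, "The Per-Protocol Set (PPS) includes patients who completed the planned treatment regimen".
- **Which set counts** (section 2.7): "Efficacy analysis will be primarily applied to the FSA and PPS". FSA is evidently a misprint for FAS.
- **Who stops early** (section 2.2.4): the grounds for termination or dropout include worsening depression and serious adverse events.

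**The concern.** Two weaknesses bear on the primary result.

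The first is timing. Membership of the FAS depends partly on judging how serious an entry violation was. If that judgement is made while outcomes and the A/B split can be seen, even by only one of those taking part, exclusions can follow the results. Knowing which code is the active drug is not necessary. Seeing that one code is ahead is enough to make some exclusions more attractive than others.

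The second is the missing hierarchy. If the FAS and PPS disagree, the article does not say which one decides. The PPS is also related to outcome: patients stopped for worsening depression or a serious adverse event do not complete the regimen, so they leave a set that stands level with the FAS.

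**Working it through.** **1. Order of events.** Section 2.6.3 gives a blinded lock with no set assignment. Section 2.3.2 then opens the A/B codes to the analyst. Section 2.8 places set assignment in the analysis phase, by the principal investigator and statistical experts. Section 2.3.2 opens treatment identity last. The order of the second and third steps is inferred by joining the two sections. Neither section states it, and neither rules it out.

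**2. The plan's own figure.** Inputs from section 2.3.3: 45.7% versus 69%, two-sided α = 0.05, power 80%, ratio 1:1. With unpooled variance, n = (1.960 + 0.842)² × (0.457×0.543 + 0.69×0.31) / 0.233² = 66.8, so 67 per group. Then 67 × 1.1 = 73.7, so 74. The stated 67 and 74 reproduce. The point does not rest on them; 74 per arm is used below.

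**3. Success on either set.** Assumptions not in the documents: a claim may be made on whichever set reaches p<0.05, and patients leave the PPS at random.

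- Bivariate normal with correlation √overlap: at 90% overlap, ρ = √0.90 = 0.949 and P(either |Z|>1.96) = 0.0648. At 85% overlap it is 0.0681.
- Simulation (100,000 runs, 74 per arm, no treatment effect, common response rate 45.7% or 57.35%, unstratified pooled z-test instead of the planned CMH test):

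| Share left out of PPS | Type I error, either set |
|---|---|
| 10% | about 0.070 |
| 20% | 0.074–0.076 |
| 30% | 0.079–0.082 |

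The FAS alone gives 0.054–0.058 in the same simulation. Its excess over 0.05 comes from the discreteness of the test.

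**4. Exclusions made with the A/B split and outcomes in view.** Pooled z-test, invented counts:

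- 45/74 versus 34/74: pooled rate 79/148 = 0.534; difference 11/74 = 0.149; SE = √(0.534×0.466×2/74) = 0.0820; z = 1.81; p = 0.070.
- Leave out two non-responders from the better arm, giving 45/72 versus 34/74: pooled rate 79/146 = 0.541; difference 0.625 − 0.459 = 0.166; SE = 0.0825; z = 2.01; p = 0.045.

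In the simulation, always dropping two non-responders from the better-looking code gives a type I error of about 0.08. Dropping four gives 0.115–0.128.

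**5. Direction of PPS bias.** Assume the planning rates hold and every patient left out is a non-responder, so that PPS rate = planning rate / (1 − share left out). The difference in all randomised patients is 69 − 45.7 = 23.3 points.

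| Left out, placebo / SGJY | Placebo rate | SGJY rate | Difference |
|---|---|---|---|
| 10% / 3% | 0.457/0.90 = 0.508 | 0.69/0.97 = 0.711 | 20.4 points |
| 3% / 10% | 0.457/0.97 = 0.471 | 0.69/0.90 = 0.767 | 29.6 points |

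The distortion can run either way.

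**The case against.** The strongest reply is that this reads much into two loose sentences.

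- **Timing.** In a condensed article, the phrase in the quality-control section may mean the analysis stage in general, including classification before any code is applied. That is possible, so the order is allowed by the text and not prescribed by it.
- **Who sees what.** A reader might infer that sets are chosen by people who know the treatment. The documents do not support that. Treatment identity stays sealed until the analysis is finished, and the first unblinding is specified only for the analyst, not for the principal investigator. What remains is that statistical experts share the allocation and nothing keeps the code-holding analyst out of it.
- **Two primary sets.** The sentence naming both sets is followed directly by the one on the safety set. It may only be matching populations to efficacy and safety, and the intention-to-treat sentence leans towards the FAS. Even so, no set is named as deciding.
- **Size.** No passage allows success on either set. If both had to be significant, the error could not exceed that of one set alone. If SGJY works, dropouts for worsening depression should be commoner on placebo, which is the case that shrinks the difference. A reader who infers that the PPS favours SGJY goes beyond the documents.
- **Matters for the SAP.** Any PPS drops non-completers, and defining a severe violation or organising a blind review is ordinary SAP content. Their absence is not the fault here. The fault is that the article does speak on timing and ranking, and what it says is unsafe on the first and open on the second.

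**Conclusion.** The point holds as a weakness in the rules as written. The plan permits set assignment after outcomes are locked and the A/B codes are open to the analyst, and it leaves no single deciding efficacy set. Confidence is moderate on the timing, because the sequence is inferred, and high on the unranked sets.

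The documents do not determine its size. The figures of about 6.5% to 7% (either set, 90% overlap) and p=0.070 moving to p=0.045 (two exclusions) are illustrations. They rest on an either-set success rule, on exclusion shares and on counts that the documents do not give. They show that a handful of judgement-based exclusions could change a borderline result. They do not show that the trial's error rate is inflated or that the result will favour SGJY. The article should be corrected before the first unblinding.

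**What to change.** 1. In section 2.8, replace the allocation sentence with: *Membership of FAS, PPS and SS is fixed and signed at a blinded data review before database lock and before the first unblinding.*
2. In section 2.7, replace the sentence on efficacy sets with: *The FAS is the sole primary efficacy set; the PPS is a supportive sensitivity analysis.*
3. Limit eligibility exclusions from the FAS to violations of criteria measured before randomisation, judged blind to group code and outcome.

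The cost is wording and one review meeting. The planned 148 patients and the data collected do not change.

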#### Termination and dropout of trial patients

2.2.4

Patients who fail to meet the inclusion criteria or fulfill any exclusion criteria.Patients with poor protocol compliance or who withdrew prematurely from the trial.Patients with incomplete medical records that hinder the evaluation of efficacy and safety.Patients whose condition deteriorated rapidly during the study, including those with acute cardiovascular events or malignant neoplasms.Patients whose depression worsens during the trial (HAMD-17 score >24 for over two weeks) or who display suicidal ideation.Patients with serious adverse events during the trial.Voluntary withdrawal by the patient.

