#### Experimental group

2.4.2

Participants in the experimental group will receive SGJY in combination with standard medical therapy. The dosage regimen is 0.36 g per pill, two pills orally, twice daily. The treatment period will last for 12 weeks. Participants will be instructed to return any unused medication and packaging at each visit to assess adherence.

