#### Follow up

2.4.5

After enrollment, all participants will undergo seven follow-up assessments. Outpatient visits will be scheduled at weeks 4, 8, and 12 post-treatment, with a ±3-day window from the start of medication administration. Additionally, outpatient or telephone follow-ups will occur at weeks 12, 24, and 36 after completion of the medication regimen.

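### The adherence formula cannot exceed 100%, so it contradicts the 80%-120% band for good adherence, and it makes no allowance for visit timing

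*Protocol article*

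**What the plan says.** Section 2.8 (Quality control) of the protocol article sets adherence by medication count. The formula is "Adherence will be calculated as follows: [(prescribed amount - unused amount)/prescribed amount] × 100" (per cent), followed directly by the classes "Good adherence: 80%-120%, Poor adherence: <80" (per cent). No class is given above 120%.

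On the count itself, 2.8 says "Before each medication dispensing, remaining study drugs and empty packaging will be collected", and 2.4.2 (Experimental group) says "Participants will be instructed to return any unused medication and packaging at each visit to assess adherence". Table 2 shows drug handed out at screening, week 4 and week 8, and collected at weeks 4, 8 and 12.

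The regimen in 2.4.2 is "two pills orally, twice daily", and "The treatment period will last for 12 weeks". On timing, 2.4.5 (Follow up) says "Outpatient visits will be scheduled at weeks 4, 8, and 12 post-treatment, with a ±3-day window from the start of medication administration".

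Section 2.2.4 lists, among the termination and dropout cases, "Patients with poor protocol compliance or who withdrew prematurely from the trial". It gives no numerical limit. Section 2.7 defines the per-protocol set (PPS) by completion of the planned regimen and does not mention the 80% cut-off.

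**The concern.** The formula and the band stand next to each other in 2.8 and do not fit. An upper limit of 120% has meaning only for a measure that can go above 100%, and this one cannot. A participant who takes more than the regimen asks for is therefore reported as an ordinary good adherer.

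Secondly, the formula contains no dates. Visits may move by 3 days either way, so the same behaviour can give different scores depending on when the capsules are counted.

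At stake is the accuracy of the only numerical adherence measure in the article. The sample size and the primary comparison do not depend on it.

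**Working it through.** **Inputs from the article.** Two capsules twice daily is 4 per day, so 28 × 4 = 112 per four weeks and 84 × 4 = 336 over 12 weeks. Visits fall at days 28, 56 and 84, each ±3 days.

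**Assumptions, because the article is silent.** Supply per visit: 28 days (112 capsules) or 31 days (31 × 4 = 124). Scoring: per dispensing interval, or once over 12 weeks. The prescribed amount is taken as the fixed supply.

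**1. Can the formula reach the stated 120%?**
Score = 100 × (prescribed − unused)/prescribed, with unused ≥ 0.
- Maximum, at unused = 0: 100%.
- For 120% on 112 capsules: unused = 112 × (1 − 1.2) = −22.4 capsules, which is impossible.

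The ceiling holds for any supply and either scoring interval.

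**2. What does over-use score?**
- Supply 124, intake at 120% of schedule for 25 days: taken 1.2 × 4 × 25 = 120, due 100, unused 4. Score 120/124 = 96.8%, *good*.
- Supply 112, all taken in 25 days: true intake 112/100 = 112%. Score 100%, *good*.

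**3. What does visit timing do to a participant who misses no dose while supplied?**

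| Scoring basis | Days | Taken | Score |
|---|---|---|---|
| One interval, 112 supplied | 28 | 112 | 100% |
| One interval, 112 supplied | 25 | 100 | 89.3% |
| One interval, 112 supplied | 31 | 112 (supply runs out) | 100%; true cover 112/124 = 90.3% |
| One interval, 112 supplied | 22 | 88 | 78.6%, *poor* |
| One interval, 124 supplied | 31 | 124 | 100% |
| One interval, 124 supplied | 28 | 112 | 90.3% |
| One interval, 124 supplied | 25 | 100 | 80.6% |
| Whole treatment, 336 supplied | 81 | 324 | 96.4% |

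The 22-day interval lies within the windows: week 4 visit at day 31, week 8 visit at day 53.

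Three days are worth 3/28 = 10.7 points on a 28-day supply, 3/31 = 9.7 on a 31-day supply and 3/84 = 3.6 over 12 weeks. The shift thus ranges from 0 (late visit, 28-day supply) to 21.4 points (22-day interval, 28-day supply). It is not symmetric: on a 28-day supply only a shortened interval lowers the score, because a late visit is capped at 100%.

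**4. Does a denominator of capsules due put this right?**
Score = 100 × (dispensed − returned)/(4 × actual days).
- Fully adherent, 25 days: 100/100 = 100%. Fully adherent, 22 days: 88/88 = 100%.
- Supply of 112 exhausted before day 31: 112/124 = 90.3%, as it should be.
- Over-use example with 124 supplied: 120/100 = 120%, instead of 96.8%.

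**5. How far can over-use then show?**
- Per interval, 112 supplied: at most 112% at day 25; above 120% only if the count falls before day 112/4.8 = 23.3 (at day 22, up to 112/88 = 127.3%).
- Per interval, 124 supplied: up to 124/100 = 124% at day 25.
- Over 12 weeks, counted at day 81: at most 336/324 = 103.7%, or 372/324 = 114.8% if each of the three supplies covers 31 days (3 × 124 = 372).

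**The case against.** The strongest reply is that only the ceiling is certain, and that the rest depends on conventions which a journal article may leave to the full protocol. Much of this stands.

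- *Visit windows.* A reader might infer that the ±3 days always move the score by about 10 points. The article does not support that. It states no supply per visit, no scoring interval, and not whether the prescribed amount means dispensed or due. If it means due by the actual date, and only capsules that were due count as unused, the timing effect largely disappears. A single early visit also leaves a perfect adherer above 80% under both assumed supplies; crossing the line takes a shorter interval or some missed doses as well.
- *Per-protocol set.* A reader might infer that misclassified participants move in or out of the PPS, or are terminated. Neither 2.7 nor 2.2.4 cites the 80% limit, and 2.8 leaves allocation to analysis sets to the principal investigator and statistical experts. Any such effect is an inference.
- *Mixed denominators.* One can build a case where 124 capsules are dispensed, 101 taken, and the 23 returned are set against 112: (112 − 23)/112 = 79.5%, against a true 101/112 = 90.2%. Nothing in the article says that counts will be made this way.
- *Limits of the remedy.* A capsule count can never show more than was dispensed, so over 12 weeks a score above 120% stays out of reach even with the better denominator.

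None of this removes the ceiling. The band could be rescued only by letting the unused amount go negative, and 2.8 describes a count of returned drug. The article prints both parts, so this is a contradiction and not an omission.

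**Conclusion.** Wrong as written, and minor. The ceiling of 100% against a band up to 120% follows from the formula alone and needs no assumption; over-use cannot register and is scored as good adherence.

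The sensitivity to visit timing is real but conditional. It is about 10 points per 4-week interval on an assumed 28- to 31-day supply, enough to label full adherence as poor in a 22-day interval (78.6%), and only about 3.6 points over 12 weeks. The documents do not establish a consequence for the PPS, for termination or for the primary result.

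**What to change.** In 2.8, define adherence as (capsules dispensed − capsules returned)/(capsules due under the regimen between the actual dispensing and return dates) × 100%. Report it for each dispensing interval and over the 12 weeks. Use three classes: below 80%, 80% to 120%, and above 120%. State that a capsule count can show over-use only up to the amount dispensed, so the top class will be reached, if at all, in the per-interval scores.

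The cost is one formula and one sentence. Dispensing, return counts and visits are already planned in 2.4.2 and Table 2. No new criterion for the PPS is needed, and nothing in the regimen or in the clinical rules changes.

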## Discussion

3

Depression may have a causal influence on the biological processes and behaviors associated with ACS, sharing several common pathological mechanisms. A bidirectional Mendelian randomization study has demonstrated a robust causal relationship between depression and an increased risk of coronary heart disease (21). Potential comorbid mechanisms include excessive immune-inflammatory response, activation of the HPA axis, endothelial dysfunction, and platelet hyperactivity (22). Depression activates the HPA axis, leading to hypercortisolemia, which is closely associated with the pathogenesis of cardiovascular diseases (23, 24). Individuals with depression often exhibit elevated levels of inflammatory markers including IL-1β, IL-6, TNF-α, and CRP, which are directly associated with acute cardiovascular events (24). Depression may also lead to immune-mediated pancreatic β-cell dysfunction, lifestyle alterations, and sustained activation of the HPA axis, resulting in visceral fat accumulation and central obesity. These factors promote insulin resistance and diabetes, both of which are significant risk factors for cardiovascular disease (25, 26). Depression has been associated with increased platelet thrombin reactivity, elevated platelet factor expression, reduced endothelial nitric oxide synthase activity, decreased serotonin transporter binding, and lower platelet serotonin levels. Enhanced platelet reactivity is believed to contribute to increased susceptibility to atherosclerotic thrombosis in individuals with depression (27). Among individuals with comorbid depression after ACS, secondary prevention strategies that prioritize mental health should be implemented. SSRIs, a class of antidepressants, are associated with numerous adverse effects. Additionally, certain antidepressants may lead to dependence and addiction, potentially resulting in poor adherence to treatment (18). Given the limited clinical treatment options, identifying safe and effective interventions for depression following ACS remains a critical challenge.

SGJY has been approved and widely prescribed in China for the treatment of depression since 2008 (20). A substantial body of clinical evidence (28–30) indicates that SGJY is more effective than conventional antidepressants and is associated with fewer adverse effects. Furthermore, preliminary studies suggest that SGJY may contribute to the prevention and treatment of coronary heart disease and exert cardioprotective effects: Extracts of *Hypericum perforatum* can reduce low-density lipoprotein cholesterol (LDL-C), alleviate oxidative stress and lipid peroxidation induced by hyperlipidemia, and are used in the prevention and treatment of atherosclerotic cardiovascular diseases. Hypericin (31), a major active constituent of *Hypericum perforatum*, has been shown to upregulate autophagy after myocardial infarction, thereby inhibiting the NLRP3 inflammasome pathway, alleviating myocardial hypertrophy, and reducing fibrinogen deposition, ultimately exerting cardioprotective effects. *Acanthopanax senticosus*, a constituent of SGJY, is widely used in the treatment of cardiovascular diseases. It protects the cardiovascular system by preserving ischemic myocardial cells, reducing reperfusion injury, inhibiting ventricular remodeling, and improving microcirculation (32). Extract of *Acanthopanax senticosus* also modulates the gut microbiota and lipid metabolism via regulation of the NF-κB signaling pathway, thereby contributing to anti-atherosclerotic effects (33). Epimedium E, another key bioactive compound in *Acanthopanax senticosus*, exhibits antioxidant, anti-inflammatory, and immunomodulatory activities. It inhibits inflammation and pyroptosis through the NLRP3/caspase-1 signaling pathway, thereby mitigating myocardial injury (34). Based on the above findings, we hypothesize that SGJY may exert beneficial therapeutic benefits in patients with depressive state after ACS. However, high-quality clinical evidence supporting this hypothesis remains limited. Therefore, we designed this trial to evaluate the clinical efficacy and underlying mechanisms of SGJY in the treatment of depressive state after ACS.

This study aims to assess the efficacy of SGJY in treating depressive state after ACS by examining series of clinical scales, inflammatory cytokines, and related proteins (IL-1β, IL-6, GDF15, and sCD40L). In addition, a 36-week follow-up will be conducted after SGJY treatment to record the incidence of MACCE and evaluate long-term prognosis. Clinical studies have shown that improvements in cardiac and pulmonary function reduce ischemic burden in patients with coronary artery disease (35), and that exercise capacity is a strong predictor of adverse cardiovascular events (36). Therefore, CPET will be included in the trial to assess patients’ cardiopulmonary endurance. Additionally, the study will measure serum levels of HPA axis-related hormones (CRF, ACTH, and cortisol) and BDNF. Upon activation of the HPA axis, the paraventricular nucleus of the hypothalamus synthesizes and releases more CRF. The CRF is transported to the anterior pituitary, where it stimulates the secretion of ACTH into the systemic circulation. ACTH acts on the zona fasciculata of the adrenal cortex promoting the synthesis and release of cortisol. HPA axis dysfunction and subsequent elevation of cortisol levels contribute to the progression of depression and an increased risk of adverse cardiovascular events (22). BDNF is a biological marker associated with depression and CHD. Reduced BDNF level is associated with an increased risk of depression in patients with ACS. Moreover, Meta-analyses have demonstrated an increase in BDNF after antidepressant treatment (37). Metabolomic analyses will be conducted to investigate the potential mechanisms through which SGJY exerts its antidepressant effects in patients with depression after ACS. GDF15 is a stress-responsive inflammatory cytokine primarily secreted by activated macrophages. Elevated GDF15 levels are closely associated with cardiovascular disease severity, increased risk of adverse cardiovascular events, and the presence of depressive symptoms (38–41). sCD40L serves as a diagnostic biomarker for atherosclerosis, a condition strongly associated with cardiovascular mortality and non-fatal myocardial infarction (42, 43). Serum sCD40L levels are also significantly elevated in individuals with depression, further increasing their risk of cardiovascular disease (44, 45).Therefore, GDF15 and sCD40L may serve as surrogate endpoints for predicting adverse cardiovascular events and may also reflect the severity of depressive symptoms.

This study has several limitations. First, the treatment period is limited to 12 weeks, with a follow-up visit scheduled 36 weeks after the end of treatment. This relatively short follow-up duration may restrict the ability to fully capture the occurrence of MACCE. This limitation elevates the risk of false-negative conclusions and consequently impairs the accuracy of evaluations regarding whether patients with ACS actually benefit from antidepressant treatment. However, previous studies have shown that biomarkers such as GDF15 and sCD40L are reliable surrogate indicators of long-term prognosis. Consequently, this trial may offer valuable insights into the potential role of SGJY in improving the prognosis of ACS. Second, CPET will be conducted by different operators across the five centers—a factor that introduces the risk of measurement variability and potential bias. Differences in test procedures, equipment calibration, or data interpretation among operators may compromise the accuracy of results and subsequent assessments of the intervention’s efficacy. To mitigate this risk, we implemented a stringent set of SOP for all CPET assessments. Furthermore, all operators and assessors received centralized, uniform training on operational and analytical protocols before the trial commenced. Third, the use of clinician-rated scales to evaluate treatment efficacy may lead to subjective bias. To ensure the reliability of the evaluation results, all researchers will undergo standardized training provided by psychiatrist before the study get started. In addition, objective biomarkers (including inflammatory cytokines, relevant proteins, HPA axis-related hormones, and BDNF) will be incorporated to support efficacy evaluation. Fourth, The use of Consensus criteria in this study may introduce over-diagnosis bias by potentially including patients who meet diagnostic criteria for Major Depressive Disorder (F32.0/F32.1) or Organic Depressive Disorder (F06.32). To address this limitation, we will perform stratified analyses by diagnostic subgroup to assess result reliability.

